#### Criteria for consideration of study termination

The trial may be stopped prior to meeting the accrual goal if the toxicity of hypo-fractionated spinal radiosurgery is determined to be unacceptable. Acute or late toxicity will be considered unacceptable if the rate of CTCAE v4.0 grade 3 toxicity is greater than 30%, grade 4 toxicity greater than 20%, or any grade 5 toxicity attributable to therapy occurs. Interim analyses of toxicity will be planned after the first 10 patients have been accrued, after an additional 20 patients, and after the total number of evaluable patients have been accrued to the study with adequate follow-up (generally > 90 days after completion of treatment) for assessment of toxicity.

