[15-20]. The most serious toxicity – radiation induced myelopathy – has been reported in less than 1% of the patients in a large analysis of > 1000 treatments
[21].

The concept of radiosurgery practiced as single fraction, however, has limitations. Due to the immediate proximity of vertebral metastases to the spinal cord, the treatment dose deliverable is limited by the tolerance of the spinal cord
[21-24]. In cases of radiosurgical treatment of these spinal cord abutting tumors, the epidural tumor component has been identified as the most frequent site of treatment failure: both the spinal cord and adjacent epidural tumour involvement were spared from high biological doses of radiosurgery
[16-18,25,26]. Consequently, many study protocols exclude tumors within a distance of < 3 mm to the spinal cord, as does the RTOG 0631 trial. This however precludes exactly those patients which are at the highest risk of cord compression.

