### Rationale for this trial

The rationale for this trial is based on the same hypothesis as the single-fraction radiosurgical studies: to improve pain control and local tumor control via dose intensified radiotherapy for vertebral metastases. This trial will differ in three important aspects from the currently available literature and trials:

1) A prognostic score for overall survival (modified Mizumoto Score) will be used for selection of patients with favourable life expectancy
[27], who are expected to benefit most from the intensified radiotherapy. The number for treatment fractions will be adjusted based on the modified Mizumoto Score to balance intensity and length of treatment with life expectancy. Selection of patients with long life expectancy will also allow for evaluation of late toxicity and long-term efficacy.

2) Hypo-fractionated radiosurgery with 5 and 10 treatment fractions will be practiced in this study. Based on radiobiological modelling, hypo-fractionated radiosurgery allows higher biologically effective doses to the tumor directly adjacent to the spinal cord than single-fraction protocols. Recurrences at the interface between the spinal cord and the epidural tumor are expected to be reduced by fractionation. This will expand the indications for dose intensified radiotherapy to tumors immediately abutting the spinal cord.

3) Failures in untreated parts of the vertebrae shall be avoided by the use of a simultaneous integrated boost concept. Similar to the single-fraction radiosurgical studies, dose intensification will be performed in the macroscopic tumour using dedicated CT and MR imaging. However, the non-involved parts of the vertebra will be treated with a second dose level (conventional dose) to avoid recurrences in the untreated parts of the vertebrae.

Preliminary results from the University Hospital Wuerzburg with dose intensified irradiation using 20 fractions of 3 Gy
[28] are promising and support the hypothesis of this trial; Patients with long life expectancy were selected for fractionated radiosurgery resulting in an actuarial local control rate and overall survival of 88% and 63% after 2 years
[13]. No acute or chronic toxicity > Grade 2 was seen.

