#### Trial duration and follow-up assessments

The primary endpoint will be pain control assessed 3 months after radiotherapy. Detailed follow-up is outlined in Table 
2. Patient follow-up will continue for five years to evaluate the secondary end points of the trial. Patient accrual is estimated to be finished within 2 years.

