## Discussion

This study will assess efficacy and safety of dose-intensified radiosurgery for painful vertebral metastases. Data from this study will help to model a potential relationship between irradiation dose and pain palliation. Such a dose–response relationship has not been demonstrated in randomized trials before: we hypothesize that irradiation doses in all arms of the randomized trials were in the flat region of the sigmoid-shaped dose–response curve and higher doses are required to improve clinical results. The modern technologies of IMRT and IGRT, which are mandatory in this study, will be used to realize planning and delivery of such escalated doses safely. Despite pain control at three months being the primary endpoint, patients will remain in follow-up for five years for analysis of long-term pain control, local tumor control and toxicity.

Follow-up was limited in the majority of the existing studies due to short overall survival of unselected patients. Patients with estimated short life expectancy will be excluded from this study, which will allow evaluation of long-term efficacy and in particular safety of intensified radiosurgery in this palliative setting. More reliable data on long-term safety with a particular focus on radiation induced myelopathy is considered highly important for further development of spine radiosurgery.

Fractionated radiosurgery allows the inclusion of patients, whose tumor actually contacts the spinal cord. Fractionation will enable higher biological doses at the target / organ-at-risk interface. This is expected to reduce the local failures, which were most likely the result of underdosing the volumes in this high-risk region. Patients with the metastases approaching the spinal cord but without neurological deficits are not typical surgical candidates and local radiotherapy with durable tumor control might be especially warranted in this patient collective for prevention of MSCC.

Fractionation might also be beneficial from a safety perspective. Despite inter- and intra-fractional patient motion being minimized by IGRT and patient immobilization devices, residual errors need to be considered and cannot fully be avoided. Fractionation is expected to limit the consequences of such errors unless they are systematic and occur on a daily basis. This will be avoided by strict quality assurance.

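### The stopping limits have no myelopathy-specific trigger: a non-fatal cord injury counts only toward pooled grade limits of 20% and 30%, at least 20 times the cited rate

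*Protocol article*

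**What the plan says.** The section Criteria for consideration of study termination allows the trial to be stopped early if toxicity is judged unacceptable, and it sets the limits by grade: "the rate of CTCAE v4.0 grade 3 toxicity is greater than 30%, grade 4 toxicity greater than 20%, or any grade 5 toxicity" (the last only if treatment is the cause). Acute and late toxicity are both covered and no type is left out. Three toxicity analyses are planned: after 10 patients, after 20 more, and "after the total number of evaluable patients have been accrued to the study with adequate follow-up", which the article generally takes as more than 90 days after treatment.

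On the cord, the Background (Radiosurgery for painful vertebral metastases) states: "The most serious toxicity – radiation induced myelopathy – has been reported in less than 1% of the patients in a large analysis". It adds that many protocols exclude tumours closer than 3 mm to the cord. This trial does the reverse. The Rationale says of fractionation: "This will expand the indications for dose intensified radiotherapy to tumors immediately abutting the spinal cord". The Discussion repeats the point: "Fractionated radiosurgery allows the inclusion of patients, whose tumor actually contacts the spinal cord". It also calls long-term safety data focused on myelopathy highly important.

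**The concern.** The limits do not fit the event the trial has most reason to watch. A limit of 20% or 30% may suit common severe toxicity. For an event cited at below 1%, a handful of cases would be alarming, yet would stay far under the limit. The cause is the height of the limits together with the lack of an event-specific trigger. Pooling over toxicity types is not the cause, because pooling makes a limit easier to cross.

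At stake is patient safety during accrual. If two or three patients suffered a non-fatal cord injury, no printed number would tell the investigators that a review is due. The third planned look falls after accrual is complete, so only the looks at 10 and 30 patients come early enough to protect later patients.

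**Working it through.** **Inputs from the article.** Limits: grade 3 above 30%, grade 4 above 20%. Looks at 10, 30 and all evaluable patients. Sample size: 54 analysable patients with 10% drop-out, 54/0.9 = 60, as the article states. Cited myelopathy rate: below 1%. Accrual: "Patient accrual is estimated to be finished within 2 years". The article gives no operating characteristics for the limits, so there is no figure of its own to reproduce here.

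**Assumptions.** Events are independent; every case is seen by the look concerned; the last look has 60 patients; there is no other toxicity of the same grade unless stated. The article does not say what grade a myelopathy would have, so all grade 4 and all grade 3 are shown as the two ends. True rates of 5% and 10% are illustrations, not expected rates; 1% is the upper end of the cited figure.

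**Step 1: counts needed to cross.** This is the smallest whole number strictly above the limit times n.

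| Look | Grade 4 (>20%) | Grade 3 (>30%) |
|---|---|---|
| 10 | 3 | 4 |
| 30 | 7 | 10 |
| 60 | 13 | 19 |

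So 2/10, 6/30 or 12/60 grade 4 myelopathies, each exactly 20%, do not cross. Against the cited rate, 20%/1% = 20 and 30%/1% = 30, so the limits are at least 20 times that rate.

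**Step 2: chance of crossing at any look.** Exact sequential binomial calculation over 10, +20 and +30 patients.

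| True rate | All grade 3 | All grade 4 |
|---|---|---|
| 1% | under 0.01% | 0.01% |
| 5% | 0.1% | 1.2% |
| 10% | 1.3% | 8.6% |

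With the first two looks only, the all-grade-4 figures at 5% and 10% are 1.2% and 8.4%. With 54 patients at the last look (11 needed), the 10% figure is 9.0%.

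**Step 3: other grade 4 toxicity.** An independent 5% background added to 5% myelopathy gives a combined rate of 1 − 0.95 × 0.95 = 9.75% and a crossing chance of about 8.0%. A 10% background gives 1 − 0.90 × 0.95 = 14.5% and about 26%.

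**Step 4: fixed numbers of cases among 60, all grade 4.** Two cases can never cross. Three cross only if all fall in the first ten patients: (10 × 9 × 8)/(60 × 59 × 58) = 720/205,320 = 0.35%.

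**Step 5: a second-case pause.** The pause can act only on cases detected while accrual is open. With f the fraction seen in time and p the true rate, the chance is P(X ≥ 2) for X ~ Binomial(60, p·f).

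| True rate | f = 1 | f = 0.5 | f = 0.25 |
|---|---|---|---|
| 1% | 12% | 4% | 1% |
| 5% | 81% | 44% | 17% |
| 10% | 99% | 81% | 44% |

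Under even accrual over 24 months and a delay of L months from treatment to detection, f = (24 − L)/24, so f = 0.5 and 0.25 correspond to assumed delays of 12 and 18 months. The article gives no latency.

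**Step 6: first-case review at a true 1% rate.** 1 − 0.99^60 = 45% if all cases are seen; 1 − 0.995^60 = 26% if half are seen while accrual is open.

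**The case against.** A reader might infer that non-fatal myelopathy has no numeric trigger at all, or that the trial would have to continue despite several cord injuries. The text supports neither. Grade 3 and 4 myelopathy counts toward the pooled limits. A fatal case meets the criterion "any grade 5 toxicity attributable to therapy occurs", which is not tied to a look. The section lists criteria for considering termination, uses permissive wording, and does not say that these are the only grounds or that stopping is confined to the planned looks. Discretionary review of a cord injury therefore remains open.

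The article also condenses a full protocol that is not shown, and rules for single serious events may be there. Prevention is addressed in print: cord dose limits in Table 1, a 1 mm cord margin, image verification to 1 mm and 1°, and exclusion of progressive neurological deficit. The only documented rate is below 1%, that is, fewer than 0.6 expected cases in 60 patients (60 × 0.01), and background grade 4 toxicity makes crossing more likely.

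All of this stands and narrows the point. It does not remove it. The article prints its own definition of unacceptable toxicity, and a pooled 20% or 30% limit is a poor guide to an event cited at below 1%. Preventive measures do not say what follows once an injury has occurred.

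**Conclusion.** The point holds as a weakness in a printed rule: there is no myelopathy-specific trigger, and the pooled limits that do apply are too high to react to a few cord injuries. If all cases are grade 4 and there is no other grade 4 toxicity, the crossing chance is about 0.01%, 1.2% and 8.6% at true rates of 1%, 5% and 10%. It is lower if cases are grade 3 or appear late, and higher with background toxicity.

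The figures above 1% show how the rule behaves; they do not forecast this trial's myelopathy rate. The article contains no miscalculation or contradiction on this point, and nothing here shows that the trial lacks safety oversight. The change is a worthwhile, cheap improvement. Confidence is medium, because the full protocol may already contain such a rule.

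**What to change.** Keep every existing grade 3, 4 and 5 limit for all toxicity, myelopathy included, and add to Criteria for consideration of study termination:

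*In addition, any attributable radiation myelopathy of CTCAE grade 3 or 4, whenever it occurs, triggers an immediate safety review. A second such case pauses accrual, if still open, pending that review.*

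State the operating characteristics as a range over f, as in step 5, because the pause loses sensitivity if onset is late: at a true 5% rate it acts with probability 81%, 44% or 17% when all, half or a quarter of cases are seen in time. After accrual closes, only the review part applies.

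**Cost.** Two sentences, with no extra patients or scheduled visits, since Table 2 already records CTCAE toxicity. Table 2 has no CTCAE assessment at 18 months (telephone pain contact only), so a late case should be reported when it presents and not held for the next visit. At a true 1% rate, the price is up to a 45% chance of at least one review and up to a 12% chance of a pause (26% and 4% while accrual is open if half of the cases appear in time).

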#### Treatment planning

Patients will be treated with a linear accelerator with beam energies varying form 6-18MV. Inversely optimized intensity-modulated radiotherapy will be mandatory. Volumetric modulated arc therapy (VMAT) will be preferably utilized compared to step and shoot IMRT to minimize treatment times.

Two different fractionations will be used depending on estimated life expectancy: patients with long life expectancy (Arm A: Mizumoto score 0–4) will be treated with 10 fractions whereas patients with intermediate life expectancy (Arm B: Mizumoto score 5–9) will be treated with only 5 fractions. Total treatment doses will be 30 Gy and 48.5 Gy at the “PTV-elective” and at the “PTV-boost” for Arm A, respectively. Total treatment doses will be 20 Gy and 35 Gy at the “PTV-elective” and at the “PTV-boost” for Arm B, respectively. Two-Gray equivalent doses (α/β = 10 Gy) at the PTV-boost are 50 Gy and 60 Gy for the 5-fractions and 10-fractions regimen, respectively. The patients will be treated on consecutive workdays, with one fraction per day.

Normal tissue dose constraints are summarized in Table 
1.

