**Table 1 T1:** **Organ**-**at**-**risk dose constraints**

	**Maximum dose**			**Mean Dose**	
	**Arm B**	**Arm A**	**Volume of max dose**	**Arm B**	**Arm A**
Fractionation Scheme	5 x 4 / 7	10 x 3 / 4.85		5x 4/ 7	10x3 / 4.85
Spinal Cord + 1 mm	23.75	35	0.1 cm^3^		
Cauda Equina	25	37.5	0.1 cm^3^		
Kidney	-	-		10	12
Bowel	24	37	1 cm^3^	-	-
Esophagus	30	40	1 cm^3^	-	-
Liver		-		12.5	17.5

Normal tissue constraints depending upon the fractionation schema.

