#### Sample size calculation

This study aims to demonstrate an improvement in pain control at 3 months from approximately 40-50% with conventionally fractionated radiotherapy to 70-80% with image-guided, hypo-fractionated radiotherapy. Assuming an improvement in pain control from 45% to 75% sample size calculations at a 5% statistical significant level show that 27 patients would be required to achieve power of the study of 90%. This is the total number of patients eligible for statistical analysis per study arm, i.e. 54 in total. Considering a 10% drop-out rate, the total number of patients is 60. No comparison will be made between the two study arms.

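### Toxicity stopping limits name no arm although two regimens are given, so a toxic arm can be averaged away, and the third look comes too late to stop accrual

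*Protocol article*

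**What the plan says.** All references are to the protocol article. The section on criteria for study termination gives the purpose of the rule: "The trial may be stopped prior to meeting the accrual goal if the toxicity of hypo-fractionated spinal radiosurgery is determined to be unacceptable". Toxicity counts as unacceptable if the rate of "grade 3 toxicity is greater than 30%, grade 4 toxicity greater than 20%, or any grade 5 toxicity attributable to therapy occurs". The first two looks are fixed by numbers of patients in the trial: "Interim analyses of toxicity will be planned after the first 10 patients have been accrued, after an additional 20 patients". The third comes "after the total number of evaluable patients have been accrued to the study with adequate follow-up", generally more than 90 days after treatment. Neither the limits nor the looks are tied to an arm.

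Other sections treat the arms as two regimens. Under Treatment planning, "Two different fractionations will be used depending on estimated life expectancy": Arm A receives 10 fractions (30 Gy elective, 48.5 Gy boost) and Arm B 5 fractions (20 Gy elective, 35 Gy boost). Table 1 sets separate organ limits by arm; for the spinal cord plus 1 mm they are 35 in Arm A and 23.75 in Arm B. The sample size section gives 27 evaluable patients for each arm: "This is the total number of patients eligible for statistical analysis per study arm, i.e. 54 in total". It plans no comparison between the arms.

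**The concern.** A rate limit is there to show early that a regimen is too toxic. With one limit over both arms, whether a toxic regimen trips it depends partly on how well the other regimen is tolerated and on how many patients happen to be in each arm. Arm is set by prognostic score and no allocation ratio is given, so the mix at each look is not controlled. Efficacy is planned by arm; the toxicity rates that could close the trial are not.

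The timing is a separate fault. The rule exists to stop the trial before accrual is complete, but one of its three looks happens after accrual is complete. At stake is the exposure of patients to a dose-escalated treatment next to the spinal cord. The efficacy conclusion is not affected.

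**Working it through.** **Inputs from the article.** Limits: grade 3 above 30%, grade 4 above 20%. Looks at 10 patients, at 10 + 20 = 30, and after all evaluable patients are accrued. Size: 27 + 27 = 54 evaluable, and 54 / 0.90 = 60 enrolled, as stated. The article gives no operating characteristics for the toxicity rule, so there is no figure of its own to reproduce here.

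**Assumptions, not in the article.** True grade 3 rates of 40% in one arm and 10% in the other; arm splits as listed below; every patient assessable at the look.

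**Trigger counts.** The trigger is the smallest count r with r/n > 0.30.

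- Whole trial: 4/10, 10/30, and 14/45 for an added look.
- By arm at 30 patients: 5/15 for equal arms; 4/10 and 7/20 for uneven arms.
- By arm at 45 patients: 7/23 and 7/22.

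**Dilution by arithmetic alone.** At 30 patients split 15/15, 9/15 = 60% and 0/15 = 0% give 9/30 = 30%, which is not above 30%. With no events in the other arm, any count from 5/15 (33%) to 9/15 (60%) exceeds the limit within its arm and passes the whole-trial look.

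**Probability of a trigger.** X and Y are the grade 3 counts in the toxic and the tolerable arm, independent binomials. The current rule triggers if X + Y ≥ 4 at 10 patients or X + Y ≥ 10 at 30. The amended rule adds X or Y at or above its own arm's count from 30 patients on, with no by-arm reading at 10. The joint distribution was enumerated exactly across looks. The first look was split 5/5 for equal arms; for uneven arms the toxic arm had 3 or 7 of the first 10.

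| True rates 40% / 10% | Whole trial only | Whole trial plus by arm |
|---|---|---|
| 15/15, by the 30-patient look | 0.297 | 0.795 |
| Toxic arm 10 of 30 | 0.115 | 0.631 |
| Toxic arm 20 of 30 | 0.534 | 0.780 |
| 15/15, then 23/22 at 45 patients (toxic arm 23) | 0.361 | 0.904 |

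For 15/15, the 0.297 is 0.212 at the first look plus 0.086 at the second.

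**Chance alarms.** Same rules, 15/15 split, equal true grade 3 rates in both arms:

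| True rate | Now, by 30 patients | Plus by arm, by 30 | Plus by arm and a 45-patient look |
|---|---|---|---|
| 10% | 0.013 | 0.035 | 0.039 |
| 15% | 0.055 | 0.146 | 0.171 |
| 20% | 0.151 | 0.342 | 0.409 |
| 25% | 0.315 | 0.569 | 0.668 |

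**Grade 4 limit, one look at 30 patients (15/15).** Triggers are 7/30 overall and 4/15 by arm. With assumed true rates of 35% and 5%, the whole-trial limit is crossed with probability 0.39; the 35% arm crosses its own limit with probability 0.83.

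**Third look.** It follows accrual of 54 evaluable patients (up to 60 enrolled) plus about 90 days, when no accrual is left to stop. The last look that can limit accrual is at 30 patients, so up to 60 − 30 = 30 enrol after it.

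**The case against.** Five points can be made for the plan.

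- **Pooling is a reading.** The article never says the rates are pooled, and a fuller protocol might tabulate toxicity by arm. This stands as a limit on certainty. But looks counted over the trial, and limits tied to the treatment concept as a whole, make the whole-trial reading the natural one. The fault lies in a rule the article states, not in detail it leaves out.
- **The scenario is unfavourable.** A gap of 30 percentage points is assumed. The article reports no toxicity above grade 2 in the preliminary series with 20 fractions of 3 Gy, and low rates of severe toxicity in radiosurgery studies. The exact pattern 9/15 and 0/15 has a probability of only about 1.3% at true rates of 40% and 10%. This is fair, but those data come from other regimens and do not exclude a toxic arm here.
- **Reading by arm raises chance alarms.** At a true 25% in both arms, still below the limit, alarms rise from 31% to 57% by the 30-patient look and to 67% with a look at 45. A by-arm grade 4 reading would add more. This stands and is the real price of the change.
- **Other protection remains.** Any attributable grade 5 event counts by itself, toxicity is recorded at scheduled visits for every patient, and stopping is discretionary. All true, but a diluted rate would not meet the written definition of unacceptable toxicity.
- **The third look has a use.** It can serve as the final toxicity assessment. That is so; the fault is listing it under a rule for stopping before the accrual goal. Under the whole-trial rule alone, an extra look at 45 adds little (30% to 36%); the gain comes from pairing it with the by-arm reading.

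**Conclusion.** The concern holds. As written, the grade 3 and grade 4 limits read as whole-trial rates and can miss an arm well above them. At assumed true rates of 40% and 10%, the chance of a trigger by the 30-patient look is 12% to 53% depending on the arm split, against 63% to 80% when the limit is also read by arm. The sizes rest on those assumed rates and splits; the 9/15 plus 0/15 example and the lateness of the third look do not. The grade 5 clause is unaffected. This should be changed because it is a cheap improvement in patient safety; confidence is medium, since pooling is inferred and not stated.

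**What to change.** Keep the present limits and the grade 5 clause. From the 30-patient look on, read the grade 3 and grade 4 limits within each arm as well as overall. State that an arm above a limit prompts review of that arm (continue, modify or close) and not an automatic stop. Add or move one look into the second half of accrual, for example at about 45 patients; failing that, state that only the first two looks can stop accrual and that the third is the final toxicity assessment.

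The cost is protocol wording, one by-arm table per look and possibly one extra look, plus the chance alarms tabulated above. That alarm rate is acceptable only because a crossing leads to review and stopping stays discretionary.
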